#### Strategies to improve adherence to interventions {11c}

Participants will be contacted privately by study investigators if they choose not to attend calls for at least two consecutive weeks and/or if they do not reach their recommended exercise dose for two consecutive weeks. This is to ensure they receive support to reach their goals and to promote adherence to the exercise components of the programme.

#### Relevant concomitant care permitted or prohibited during the trial {11d}

Participation in another fall prevention programme for the duration of the trial will not be permitted.

#### Provisions for post-trial care {30}

If participants become upset or distressed as a result of participation in the research project, the research team will be able to arrange for counselling or other appropriate support. Any counselling or support will be provided by qualified staff who are not members of the research team. This counselling will be provided free of charge. Alternatively, a number of free contactable support services are included on the participant information sheet.

### Outcomes {12}

The primary outcome is psychological distress, and secondary outcomes include physical activity levels, social capital, cognition, concern about falling, loneliness, quality of life, physical functioning and exercise enjoyment. Participants will complete all questionnaires at baseline, week 11 (post-intervention) and at the 1-month follow-up point (see Table 3) so that change from baseline to post-intervention and change from baseline to the follow-up point can be evaluated. It will take approximately 45 min for participants to complete questionnaires at each time point. A demographics questionnaire will also be completed by participants at baseline only. This will ask participants about their age, the highest level of education completed, marital status, living situation, employment status, known medical conditions, their mobility around the house and outdoors, fall history, self-reported concern about falling and Facebook usage.

**Table 3 Tab3:** Timeline for data collection

	Pre-programme		Programme	Post-programme	
	Enrolment (< − 1 week)	Baseline (− 1 week)	Weeks 1–10	End of week 10	Follow-up (+ 4 weeks)
**Eligibility screen**					
Demographics questionnaire	X				
PA vital sign	X				
Ottawa 4DY	X				
SIDAS	X				
Informed consent		X			
**Assessments**					
Pre-programme tool		X			
K10	X	X		X	X
IPEQ		X		X	X
Cognitive Brain Games Battery		X		X	X
Social Capital Questionnaire		X		X	X
EQ-5D		X		X	X
UCLA Loneliness Scale		X		X	X
Functional component of the Late Life Function and Disability Instrument		X		X	X
Icon-FES		X		X	X
PACES		X		X	X
**Adherence**					
Average weekly *StandingTall* training duration (recorded by the app and monitored following data transfer to the server)				X	
Total *StandingTall* training duration (recorded by the app and monitored following data transfer to the server)				X	
Facebook post views (recorded by Facebook)				X	
Average weekly training frequency and duration of individualised aerobic and strength programmes (participant survey)				X	

*PA*, physical activity; *Ottawa 4DY*, Ottawa ‘day, date, world, year’; *SIDAS*, Suicidal Ideation Attributes Scale; *K10*, Kessler 10; *IPEQ*, Incidental and Planned Exercise Questionnaire; *European EQ-5D*, Quality of Life five dimensions; *Icon-FES*, Iconographic Falls Efficacy Scale; *PACES*, Physical Activity Enjoyment Scale

### Participant timeline {13}

Figure 1 illustrates the participant flow through the trial.

**Fig. 1 Fig1:**
[figure not shown]
Chart shows the participant flow through the study and intervention process

### Sample size {14}

#### Power calculation

A power analysis was conducted using GLIMMPSE [34] based on pilot data [19] to estimate the variance for this larger study [35]. To get an estimate of the variance of psychological distress (K10), the sum for the three time point (pre, post and follow-up) K10 measures were calculated. Then, a mixed model with common error variance for the time points and a compound symmetric covariance matrix was run.

A sample size of *n* = 68 is required, assuming SD = 6.41, correlation between repeated values of 0.6 and 80% power to detect a moderate effect. Allowing for a dropout rate of 15%, the total sample required is *N* = 80. This sample size is comprised of the following samples from each of the participant groups:Participant group 1 (intervention): 40Participant group 2 (waitlist control): 40

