### Eligibility criteria {10}

Individuals will be considered eligible if they meet the following inclusion criteria: (i) aged 60+ years; (ii) proficient in written and spoken English; (iii) living independently in the community, in Australia; (iv) able to mobilise indoors without the use of a walking aid; (v) have access to the Internet at home, Facebook and either computer, laptop or iPad/tablet access; and (vi) self-reported to be currently participating in less than 150 min of moderate to vigorous intensity physical activity per week through the use of the Physical Activity Vital Sign Questionnaire [31].

Individuals will be excluded from the study if (i) they have high levels of psychological distress (score of > 30 on the K10) unless deemed to have support from a mental health professional or (ii) they have a high risk of suicidal behaviour (score of > 21 on the SIDAS) unless deemed eligible to participate by a clinical psychologist through a suicide risk assessment. Other exclusion criteria are (i) absolute contraindications to exercise according to the American College of Sports Medicine (ACSM) or relative contraindications without medical clearance to exercise [32], (ii) currently participating in a fall prevention programme at least weekly, (iii) signs of cognitive impairment (score < 4) as assessed by the Ottawa 3DY or (iv) diagnosis of a progressive neurological condition.

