## Statistical methods

### Statistical methods for primary and secondary outcomes {20a}

Data analysis using IBM SPSS 25 will evaluate whether there are any significant changes between baseline and post-intervention on psychological distress and secondary outcomes, as well as between baseline and results at the follow-up point. Linear mixed models will be applied for each outcome measure, excluding physical activity, conducted using the MIXED procedure (considering data at all time points). A generalised linear mixed model with appropriate distribution will be used to analyse physical activity, measured by the IPEQ. Time will be considered a categorical variable for each outcome. Effect sizes (Cohen’s *d* and the 95% confidence intervals) will be calculated to determine the size of the within-group change between before and after treatment and between before treatment and 1-month post-intervention. Time, group and the interaction between these will be used as predictors. Marginal means drawn from the mixed models will be used.

Analyses will use all available data as per an intention-to-treat approach. The between-group difference at post-intervention and follow-up from baseline [mean difference (MD) and 95% confidence interval] will be calculated for all outcome measures using a baseline-adjusted mixed model with group as the independent variable, post-programme (week 10) and also follow-up (week 14) score on the outcome measures as the dependent variables, baseline score on the outcome measure as a covariate, and statistical significance set at *P* < 0.05. The results and effects will be reported as unadjusted and adjusted for sex and age. Time, group and the interaction between these will be used as predictors.

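### The 80% power claim names no effect size or contrast; if moderate means 0.5 SD, the planned baseline-adjusted comparison at one time point has about 72% with 68 analysed

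*Protocol article*

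**What the plan says.** In the protocol article, the section Power calculation reports a GLIMMPSE analysis based on pilot K10 data at three time points, for which "a mixed model with common error variance for the time points and a compound symmetric covariance matrix was run". It concludes that "68 is required, assuming SD = 6.41", with "correlation between repeated values of 0.6 and 80% power to detect a moderate effect". A 15% dropout allowance takes 68 to 80. The paragraph does not put a number on the effect, in K10 points or SD units. It also does not name the test or time point, alpha, or sidedness.

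The section Statistical methods for primary and secondary outcomes {20a} plans mixed models with time, group and their interaction. It then reports the between-group difference at post-intervention and at follow-up, each with a 95% confidence interval, from a model with "baseline score on the outcome measure as a covariate" and "statistical significance set at *P* < 0.05".

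Table 3 schedules the K10 at enrolment and again at baseline. Under Eligibility criteria {10} the K10 also serves as a screen (exclusion for a "score of > 30 on the K10", with an exception). Under Sequence generation {16a}, randomisation follows screening and all baseline measures, so both scores precede allocation. The analysis section names one baseline score and gives the enrolment score no role.

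**The concern.** The effect size drives the sample size, and it is the one input that the paragraph leaves as a word. The SD of 6.41 does not fill the gap: if the effect is meant in SD units the SD cancels, and if it is meant in K10 points no such figure is given. The usual reading of moderate is d = 0.5, and the analysis section itself uses Cohen's d. On that reading, 68 analysed does not match the two-sided per-time-point comparison that is planned.

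At stake is how a null result is read. A reader who takes the paragraph at face value would assume a 20% chance of missing a half-SD effect. For the per-time-point baseline-adjusted comparison that chance is about 28%. The reader also cannot see which K10 difference the trial was built to detect.

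**Working it through.** **Inputs.** From Power calculation: 68 analysed (34 per arm at 1:1), SD 6.41, ρ = 0.6 with compound symmetry, power 80%, dropout 15%. From the analysis section: alpha 0.05, taken as two-sided because 95% confidence intervals are reported. Assumption: moderate is d = 0.5, that is 0.5 × 6.41 = 3.2 K10 points; a range follows below.

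**The plan's own figure.** The dropout step reproduces: 68 / 0.85 = 80. The 68 itself cannot be reproduced, because its effect and contrast are not given.

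**Method.** With the outcome in SD units, a between-group contrast with variance factor v has SE = √(4v/68). Power comes from the noncentral t distribution with noncentrality d/SE.

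- Baseline-adjusted, one time point: v = 1 − ρ² = 1 − 0.36 = 0.64. SE = √(2.56/68) = 0.194, noncentrality 0.5/0.194 = 2.58, power 71.9%. For 80%, 84 analysed are needed (84/0.85 = 99 with dropout).
- Baseline-adjusted average of both follow-ups: residual covariance 0.6 − 0.36 = 0.24, v = (0.64 + 0.24)/2 = 0.44, power 86.5%.
- Time-by-group test, 2 df, all three time points: changes from baseline have variance 2(1 − 0.6) = 0.8 and covariance 0.4. For effects (0.5, 0.5), λ = 17 × 0.25 × 0.8/0.48 = 7.08, power about 65%, with 96 needed for 80%. For (0.25, 0.5), λ = 17 × 0.3125 = 5.31, power about 51%.
- Baseline-adjusted joint 2-df test of both follow-ups, equal effects: λ = 17 × 0.5/0.88 = 9.66, power 78%.

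**Sensitivity to the meaning of moderate** (baseline-adjusted, one time point, 68 analysed):

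| d | K10 points | Power |
|---|---|---|
| 0.40 | 2.6 | 53% |
| 0.45 | 2.9 | 63% |
| 0.50 | 3.2 | 72% |
| 0.55 | 3.5 | 80% |
| 0.60 | 3.8 | 86% |
| 0.70 | 4.5 | 94–95% |

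The 80% point is d = 0.552, or 0.552 × 6.41 = 3.5 points. With all 80 analysed, power at d = 0.5 is 79%.

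**Which calculations give about 68 at 0.5?** Two of the variants tried do: a one-sided 5% baseline-adjusted test at one time point (66 needed; 81.7% with 68), and a within-arm paired test of a standardised change of 0.5 (34 per arm, 80.8%). Neither is the planned two-sided between-group comparison.

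**Using both pre-randomisation K10 scores.** If their mean is the covariate and the two scores correlate r, v = 1 − 2ρ²/(1 + r) = 1 − 0.72/(1 + r). The documents do not give r, so a range is shown, at d = 0.5 with 68 analysed:

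| r | v | Power |
|---|---|---|
| 0.6 | 0.55 | 78% |
| 0.7 | 0.576 | 76% |
| 0.8 | 0.60 | 75% |
| 0.9 | 0.621 | 73% |

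**The case against.** A reader might infer that the 80% is simply wrong and that the true power is 62–72%. The documents do not support that. No numeric effect is stated, and at d = 0.55, about 0.3 K10 points above the assumed 3.2, the per-time-point comparison does have 80%. The 62% belongs to an unadjusted change-score contrast (v = 0.80), whereas the analysis section attaches its significance level to the baseline-adjusted model.

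The calculation was also a repeated-measures one, so a different hypothesis may have been powered. A joint baseline-adjusted test comes within 2 points of 80%. The group main effect in the planned model corresponds to the average over both follow-ups, at about 86%. This stands: no single power figure can be assigned to the paragraph. It does not clear the paragraph, because neither contrast is named there and the reported differences are per time point.

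The planned confidence intervals will show which K10 differences a null result excludes, which limits the harm but does not make the stated power checkable.

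A reader might also take the unused enrolment K10 for an error. It is not; one baseline covariate is a legitimate choice. The two scores are taken close together, so r may be high and the gain small, and the screening cut-off may restrict their range. Because both precede randomisation, using them introduces no bias.

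**Conclusion.** The point holds in conditional form. The sample-size paragraph claims 80% power without the effect or the contrast, so its 68 cannot be verified. If moderate means 0.5 SD, the planned two-sided baseline-adjusted comparison at one time point falls about 8 percentage points short, and the time-by-group test falls 15 to 29 points short. These figures rest on d = 0.5, two-sided 5%, compound symmetry with ρ = 0.6, and 68 analysed. A demonstrated arithmetic error would be too strong a description. The enrolment K10 is a missed efficiency worth roughly 1–6 points of power, secondary to the main point.

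**What to change.** 1. Rewrite the sample-size paragraph to give the effect in K10 points, the contrast and time point, alpha and sidedness, and the power that contrast has. For the per-time-point comparison it could read: 68 analysed give 80% power (two-sided 5%) for a baseline-adjusted difference of about 3.5 K10 points (0.55 SD) at one time point, and about 72% for 0.5 SD. If another contrast was powered, report the actual GLIMMPSE inputs and name that contrast instead.

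2. Optionally, prespecify the mean of the enrolment and baseline K10 as the baseline covariate for the K10 analysis, raising per-time-point power at 0.5 SD from 72% to about 73–78%.

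The first change costs only text, although the stated power may look less favourable. The second uses data already scheduled. Trial status reports recruitment and data collection as complete, so neither change involves enrolling more; the second should be documented before outcomes are analysed by group.

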#### Recruitment {15}

Participants will be recruited through targeted online and print advertisements. The recruitment advertisement will also be posted on the social media accounts of study investigators, Facebook advertisements and news outlets targeting the 60+ year age group. Interested individuals will respond through a website called JotForm. They will follow a link to a private webpage and by entering their contact details into a form, consent to being contacted by the study investigators to provide a participant information statement and consent form.

#### Assignment of interventions: allocation

##### Sequence generation {16a}

Randomisation will use randomly permuted block sizes of 2, 4 and 6 within an online REDCap database. Participants will be allocated (1:1) to either the intervention or waitlist control group after they have been screened for eligibility, provided consent and completed all baseline measures. Participants in the same household will be considered one unit for this process.

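### Co-residents are randomised as one household unit, but the described models and the sample size have no household level; if co-residents enrol and their outcomes correlate, standard errors will be somewhat too small

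*Protocol article*

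**What the plan says.** Under Sequence generation {16a} the protocol article sets individual 1:1 allocation ("Randomisation will use randomly permuted block sizes of 2, 4 and 6 within an online REDCap database") with one exception: "Participants in the same household will be considered one unit for this process". Where two or more participants live together, the randomised unit is therefore the household.

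Under Statistical methods for primary and secondary outcomes {20a} the analysis is described as follows: "Linear mixed models will be applied for each outcome measure, excluding physical activity, conducted using the MIXED procedure", with a generalised linear mixed model for physical activity. On the terms in the model it says "Time, group and the interaction between these will be used as predictors". Baseline score enters the between-group model as a covariate, and "The results and effects will be reported as unadjusted and adjusted for sex and age". The test level is given as "statistical significance set at *P* < 0.05". The section names no random effect or covariance structure, and no household term or cluster-robust standard error appears there or elsewhere in the article.

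The Power calculation section requires 68 people, "assuming SD = 6.41, correlation between repeated values of 0.6 and 80% power to detect a moderate effect", and then: "Allowing for a dropout rate of 15%, the total sample required is *N* = 80". The only correlation in it is between repeated measurements on the same person.

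**The concern.** Two parts of the stated design do not meet. The allocation rule departs from individual randomisation for co-residents; the model description and the sample size do not reflect that departure. For participants who share a home, this is cluster allocation with clusters of two or more.

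When members of a cluster always share an arm, positive correlation between them adds to the variance of the arm mean. An analysis that treats them as independent leaves that extra variance out. Its confidence intervals are then too narrow and its test is anti-conservative. Positive correlation between co-residents is plausible for distress (the primary outcome), loneliness, social capital and physical activity, and co-residents in the intervention arm would also go through the programme together. The trial is sized for 80% power with no allowance for this.

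**Working it through.** **The plan's own figure.** 68 / (1 − 0.15) = 68 / 0.85 = 80, so the dropout step reproduces. The 68 itself cannot be confirmed, because the moderate effect is given no number; that is a separate matter and does not affect what follows. The step from 68 to 80 allows for dropout only.

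**Inputs.** From the article: n = 68 evaluable, 80 in total, 80% power, level 0.05 (taken as two-sided). Not in the article, and therefore assumed: the share *s* of participants who are in two-person study households, and the within-household correlation ICC of the outcome after baseline adjustment.

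**Formulas.** Each paired participant adds one covariance term to the variance of the arm mean, so

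- design effect DE = 1 + *s* × ICC
- model standard error / true standard error = 1 / √DE
- true type I error = 2 × [1 − Φ(1.96 / √DE)]
- effective sample size = 68 / DE
- power of a correctly calibrated test = Φ((1.96 + 0.842) / √DE − 1.96)

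**Results.**

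| *s* | ICC | DE | SE too small by | true type I error | effective n of 68 | power |
|---|---|---|---|---|---|---|
| 0 | any | 1.00 | 0% | 5.0% | 68 | 80% |
| 10% | 0.2 | 1.02 | 1.0% | 5.2% | 66.7 | 79.2% |
| 20% | 0.3 | 1.06 | 2.9% | 5.7% | 64.2 | 77.7% |
| 40% | 0.4 | 1.16 | 7.2% | 6.9% | 58.6 | 73.9% |
| 50% | 0.5 | 1.25 | 10.6% | 8.0% | 54.4 | 70.7% |

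For example, at *s* = 40% and ICC = 0.4: DE = 1 + 0.4 × 0.4 = 1.16; √1.16 = 1.077; 1.96 / 1.077 = 1.82; two-sided tail area 0.069. The last row is an outer bound beyond the range used for the conclusion.

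**Check by simulation.** Eighty people, households randomised, a plain two-sample t test, 15,000 runs per setting. With no shared households the rejection rate was 0.049 to 0.050. At ICC 0.3 it was 0.0525 (*s* = 10%), 0.0561 (20%) and 0.0693 (50%), against 0.0535, 0.0570 and 0.0676 from the formula. The highest value, at *s* = 50% and ICC 0.5, was 0.082. The formula and the simulation agree to within simulation error. The simulation used a single outcome, with ICC standing for the correlation that remains after adjustment; it did not fit the trial's mixed model.

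**The case against.** The strongest reply is that {20a} lists fixed terms only. It names no random effect, not even a participant intercept, and the compound symmetric matrix belongs to the pilot-data model used for the power calculation. A reader might infer that the article fixes a model that handles repeated measures within a person and nothing else. The text does not say that. A household random effect is not a predictor in the sense used there, and it could stand in an analysis plan that is not shown. This stands as a limit on the claim. It does not remove the point: the article discloses an unusual randomisation unit, describes the model at some length and does not connect the two. The sample size is also a finished calculation without a household level.

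Second, a reader might infer that the standard errors are too small, and the false-positive rate above 5%, as a matter of fact and for every outcome. The documents do not support that. Nothing says how many co-residents enrolled. Under Recruitment {15} people respond individually to advertisements, and under Eligibility criteria {10} each must qualify separately, so the household rule may be no more than a contingency. Nor is there a particular argument for correlation on the cognitive tasks or physical functioning.

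Third, baseline adjustment should remove part of any stable likeness between co-residents, so a correlation of raw scores would overstate the problem. That is right, and it is why the correlation assumed above is the residual one. Adjustment may reduce it but does not guarantee that it is zero.

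**Conclusion.** The point holds in conditional form. The article randomises co-residents as one unit, and neither its described models nor its sample size has a household level. If co-residents enrol and their baseline-adjusted outcomes are positively correlated, analysis as described gives standard errors that are somewhat too small and a test that is somewhat anti-conservative.

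The size is modest. With 10% to 40% of participants in pairs and a residual correlation of 0.2 to 0.4, both assumed, the design effect is about 1.02 to 1.16, the true type I error about 5.2% to 6.9%, and the effective size of 68 falls to about 67 to 59. At the lower end this is negligible; at the upper end it could matter for a primary result close to the threshold. With no shared households or no residual correlation there is no effect. It is worth correcting because the correction is cheap, not because the trial's conclusions are shown to be at risk.

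**What to change.** Add a random intercept for household, with participants nested in household, to the mixed models for the primary and secondary outcomes, including the generalised model for physical activity. State in advance that household-clustered robust standard errors will be used if the household variance is estimated at zero, which is a real possibility with few pairs. Report the number of shared households and of participants in them, by arm, so that readers can judge the effect.

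The cost is one line per model and slightly wider intervals. No new data are needed, because household membership had to be known to apply the allocation rule. Data collection is complete according to Trial status, so the sample size cannot be revised; the change is to the analysis and its reporting only.
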